**Following criteria is used in patient selection:**

Inclusion criteria:

- low energy intra- or extra-articular dorsally displaced DRF within 3cm of the radiocarpal joint, diagnosed with lateral and posterior-anterior radiographs in emergency room (ER)
- physician on call (general practician (GP), acute physician, orthopedic resident or orthopaedic consultant) thinks patient could be appropriate for conservative treatment

Exclusion criteria:

- Operative treatment
- Refuse to participate the study
- Open fracture more than Gustilo 1 gradus
- Age 64 or less
- Chauffeure’s or Barton´s fracture
- Smith´s fracture (volar angulation of the fracture)
- Does not understand written and spoken guidance in local languages
- Pathological fracture or (previous) fracture in the same wrist, antebrachium or elbow
  1. **RANDOMISATION**

All patients will be randomized before closed reduction of displaced fractures and immobilization without reduction of non-displaced fractures to either functional cast or flexion-ulnar deviation cast for 5 weeks. Patients will be randomized using a random number matrix in block allocation fashion. The blocks will be stratified by the known associations; age, centre and intra or extra-articular fracture line. The treatment allocations from the matrix will be sealed in envelopes, which are located in the ER. After the patient´s enrollment has been confirmed and informed consent is signed, a medical orderly specialized in casting will open the envelope and make the cast as allocated. The medical orderlies responsible for the casting will not participate in other ways in the study.

The research coordinator will monitor the study flow. An independent monitoring committee has been established.

- 1. **INTERVENTION**

DRFs are in everyday life treated by health care center physicians, experienced acute physicians, and trauma surgeons, thereby; we do not see any reason to limit the number of on call physicians or education or experience of on-call physician in this pragmatic trial.

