Closed reduction is done under local anaesthesia by injecting Lidocaine 1% into fracture area. The technique of closed reduction is not limited to any specific technique. Fluoroscopy can be used when performing closed reduction if it is available in the participating center. Cast reduction position examples are delivered to participating centers to assure correct position of casting. After closed reduction, additional radiographs will be taken to confirm the reduction of the fracture. After physician on-call has accepted the fracture to be treated conservatively, a dorsal splint for 5 weeks is used. Non-displaced fractures are immobilized according to randomization without reduction.

After the allocation and preparing the cast, the patient is asked to fill the PCS questionnaire.

- 1. **FOLLOW-UP**

Follow-up visits are being conducted in primary health care centers as seen necessary by the physician on-call. They are arranged by the regional guidelines, at 1 and 2 weeks with radiographs. Due to the pragmatic nature of the trial we will not set any angulation degrees or shortening limits indicating operative treatment if reduction is lost during the follow-up. Whether the achieved angulation and/or possibly restored shortening is lost during the follow-up, the decision to consult local orthopedist or hand surgeon is left to the discretion of treating physician. Moreover, if patient has been referred for operative treatment from the primary care by the physician on-call but conservative treatment is chosen in the referral center ,the patient is still eligible for the study. Follow-up of these patients is conducted in the primary care or hospital based on local protocols. Since patients will be randomized in blocks by the hospital, we will assume that randomization will take care of the possible differences between centers.

**Figure**: Flow chart of the trial.

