In this trial, a validated wrist specific PRWE-score is used as the primary outcome measure. Just recently Wallenkamp and coworkers published a report, where minimal clinically important difference in PRWE was set at 11 points with SD of 14 [37]. Based on power calculations (Cl 95%, power 0.95, SD 14) required sample size per group is 40 patients. Assuming 30% of drop-out due to possible surgical interventions during cast treatment, group size would be 52 per group (total 104). In case of patient cross-over, patients will be analyzed according to the intention-to-treat principle.

- 1. **ANALYSIS OF THE MATERIAL**

Each patient will get an initial trial identification number (TIN) which is matched with actual patient identification (ID). **The matching key is stored in study nurse’s office in Tampere University Hospital. Patients are handled only with TIN during follow-up period and analyzing the of the material. Results are given only in general level with mean values thus individual patient’s information is not able to be extracted. The electronical registry contains x-rays and it is located in hospital’s secure server. The research data will be deleted 15 years after the end of the study.**

- 1. **STATISTICAL ANALYSIS**

Continuous skewed variables between the groups were compared by the Mann-Whitney *U* test and t-test is used when variables are unskewed. Results are presented with 95% confidence intervals. Two-way-tables with the chi-square test will be used for dichotomous variables. In subgroup analysis the effect of age, sex, fracture group, smoking, and other diseases will be evaluated against the scores and overall quality of life after fracture.

Analysis of covariance will be used to assess the effect of pain catastrophizing score on the outcome of cast treatment. PRWE will be used as a dependent variable, cast as independent and pain catastrophizing score as covariate.

The effect of cast position and PRWE is investigated also in the multivariate manner. Multivariable analysis is performed with linear regression analysis since the outcome variable PRWE is normally distributed. Main variable of interest included is the cast and age, sex, fracture group, smoking and other diseases are used as confounding variables.

- 1. **ETHICAL ISSUES**

The ethical approval of this study is applied with this research plan.

1. **IMPLEMENTATION**
   1. **CONTINGENCY PLAN**

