In Finnish population aged 60 years or more the incidence of DRF can be estimated to be 126-190 per 100 000 person years [38,39]. We need to recruit more than 100 patients as suggested by the power calculation. Time for accrual in a single center is estimated to be too long; therefore to be able to enroll sufficient number of patients we are conducting a multicenter study. This study will be carried in Tampere University hospital, in Central Finland Central hospital and Satakunta Central hospital. Tampere has a catchment area with a population of 300 000 people who in case of an emergency are referred to emergency department located in the Tampere University hospital. The two latters have a catchment area with a population of 100 000 to 150 000 people who are referred to Central Finland and Satakunta Central hospitals in case of an emergency. With the incidence indicated above, we’ll identify 650-950 DRFs among elderly patients aged 60 or more within one year. Therefore we assume to finish recruiting study patients within one year.

We have homogeneity between centers with solid trial designs, data and project management including monitoring. A site personnel training has been carried out. We have been assisted by local research centers. Stability of the trial has been maintained with regular mails where researchers have shared concerns, problems and successes. Regular annual meetings (twice a year, previous on Jan 15, 2016 in Stockholm) will motivate the research team and maintain stable quality in treating. Meetings also include presentations of future studies and trials, methodology and scientific meanings will be debated. Homepage of the research team including current trial (www.nitep.eu) is under coding.

1. **Expected results and impact**
2. We expect to observe better functional outcome after functional cast treatment compared to flexion -ulnar deviation retention cast
3. We expect to observe better grip strength, quality of life, less cast changes and smaller pain in VAS with functional cast compared to flexion-ulnar deviation retention cast
4. Functional outcome is assumed to correlate with PCS regardless of treatment modality
5. After publishing these results we aim to support the creation and dissemination of trustworthy guidelines by health authorities and professional organizations.

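### Randomisation is stratified by centre, but no listed analysis of PRWE includes centre, and the PRWE test is left open between t-test and Mann-Whitney

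*Protocol*

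**What the plan says.** **Randomisation.** The Randomisation section of the protocol states: "The blocks will be stratified by the known associations; age, centre and intra or extra-articular fracture line". The Contingency plan names three hospitals: "This study will be carried in Tampere University hospital, in Central Finland Central hospital and Satakunta Central hospital".

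**Centre.** The Follow-up section notes that randomisation is blocked by hospital and concludes that "we will assume that randomization will take care of the possible differences between centers".

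**Analysis.** The Statistical analysis section lists three analyses that bear on PRWE:
- A two-group comparison without covariates. The rule is "Continuous skewed variables between the groups were compared by the Mann-Whitney" U test, and "t-test is used when variables are unskewed". It gives no criterion for skewness and names no test for PRWE.
- An analysis of covariance of PRWE with cast and the pain catastrophizing score only.
- A linear regression, introduced as follows: "Multivariable analysis is performed with linear regression analysis since the outcome variable PRWE is normally distributed". On its covariates the section says: "Main variable of interest included is the cast and age, sex, fracture group, smoking and other diseases are used as confounding variables".

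Centre is in none of the three.

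**Sample size.** The Power analysis section uses a mean difference of 11 PRWE points with SD 14.

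**The concern.** There are two linked problems.

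First, blocking within strata forces the arms to be nearly balanced on centre, age and fracture line. Variation between strata then largely drops out of the difference between casts. An unadjusted test still counts that variation in its standard error, so the reported interval is wider than the real uncertainty. The Follow-up section's argument on centre is sound for bias but not for the standard error: balance by design is the reason to put the factor in the model.

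Second, the section describes PRWE in two ways that do not fit together. If PRWE is known to be normal, the skewness rule has no role for it. If it is not known, the stated reason for linear regression fails. The protocol does not say which holds. The main comparison could therefore end as a mean difference or as a rank comparison, and only the first can be set against the 11 points.

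At stake are some precision and a primary analysis that is fixed before results are seen.

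**Working it through.** **1. The plan's own figure.** For two means, n per group = 2 × [SD × (1.96 + 1.645) / 11]² = 2 × (14 × 3.605 / 11)² = 42.1, so 43 (two-sided 5% assumed, power 0.95). The protocol gives 40. With 40 per group the power is 0.940 by the normal formula and 0.935 by the t distribution. That small gap is a separate matter. It is used here only to anchor the simulation, which should give about 94% when the strata have no effect.

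**2. Effect on the standard error.** Let R² be the share of PRWE variance explained by the strata. With the arms balanced within strata:
- true SE of the difference ≈ SD × √(1 − R²) × √(2/n)
- SE reported by the unadjusted t-test ≈ SD × √(2/n)
- ratio = 1/√(1 − R²); approximate type I error = 2 × Φ(−1.96 × ratio)

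The protocol gives no R², so it is assumed. With 52 per arm, 14 × √(2/52) = 2.75.

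| R² | Adjusted SE | Ratio | Type I error, unadjusted |
|---|---|---|---|
| 0 | 2.75 | 1.00 | 5.0% |
| 10% | 2.60 | 1.05 | 3.9% |
| 20% | 2.46 | 1.12 | 2.8% |

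Simulation with 52 per arm, 12 strata and blocks of 4 agrees. At 10% the SEs are 2.74 unadjusted and 2.61 adjusted (5% too large), with type I error 4.3%. At 20% they are 2.75 and 2.47 (11% too large), with type I error 2.7% and 3.6% in two separate runs. At 0% they are 2.74 and 2.75.

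**3. Power at the protocol's own difference.** This simulation has 80 analysed patients (40 per arm), three centres, two age bands, two fracture types, blocks of 4, total SD 14 and 3,000 trials per case. Age bands, block size and centre shares are assumed, because the protocol does not give them. The first column shows variance explained by centre plus variance explained by age and fracture type.

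| Variance explained | Measure | t-test | Mann-Whitney | Age and fracture, no centre | All three factors |
|---|---|---|---|---|---|
| 0 + 0 | type I error | 5.7% | 5.3% | 5.6% | 5.7% |
| | power | 93.9% | 92.9% | 94.0% | 93.8% |
| 5% + 5% | type I error | 3.9% | 3.9% | 4.0% | 4.4% |
| | power | 93.9% | 93.1% | 94.7% | 95.4% |
| 10% + 10% | type I error | 3.3% | 3.1% | 4.0% | 5.2% |
| | power | 95.5% | 94.5% | 96.5% | 97.5% |
| 20% + 10% | type I error | 2.1% | 2.4% | 2.8% | 5.9% |
| | power | 96.1% | 94.7% | 97.2% | 98.8% |

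Simulation error is about ±0.8 points on a 5% rate (1.96 × √(0.05 × 0.95 / 3000)). From the t-test to the full model the power gain is 1.5, 1.9 and 2.7 points in the last three cases. From the model without centre to the full model it is 0.7, 0.9 and 1.6 points. The 0 + 0 row matches the anchor in step 1.

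**4. The skewness rule.** Both arms were drawn from the same distribution, 40 per arm, 6,000 trials, with a skewness test at 5% as an assumed trigger. Switching tests rejected in 5.4% (normal), 5.0% (exponential) and 4.9% (gamma, shape 3) of trials. So switching does not inflate type I error when the distributions are equal. The defect is that the quantity estimated is not settled in advance.

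**The case against.** The other side has a good deal to say.

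- **The regression already does much of this.** It includes age and fracture group, carries no skewness condition, and its cast coefficient is an adjusted mean difference in PRWE points with a 95% interval. This stands. It is therefore too broad to say that the whole analysis ignores the stratification. That is true of the two-group tests and the analysis of covariance. In the regression only centre is clearly missing, although fracture group is not defined as the intra- or extra-articular factor.
- **Randomisation within hospitals prevents confounding by centre.** This also stands; only precision is affected. A reader might infer that the intervals are invalid or the false-positive rate raised. The error runs the other way: the unadjusted test is conservative.
- **Stratum effects may be small.** The Contingency plan claims homogeneity between centres, and the protocol calls the factors known associations without saying with what. At 0% there is no loss. But the Intervention and Follow-up sections leave reduction technique open and let fluoroscopy and some follow-up vary locally, so a centre effect is plausible, and adjusting costs almost nothing if there is none.
- **The skewness rule is general, and PRWE is called normal, so PRWE goes to the t-test.** This is a fair reading, but it rests on a distribution asserted before data exist. That skewness would be judged on the observed data is itself an inference, though the text offers no other basis. A reader might also infer a high false-positive rate from examples with equal means and different shapes. Such examples need unequal distributions and an invented trigger, and rejection there is not an error under Mann-Whitney's own null hypothesis.
- **These are details for a statistical analysis plan.** They could have been left to one, but the protocol itself sets the test rule and the covariate list and gives a reason for treating centre as dealt with.

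**Conclusion.** The point holds as a modest one about precision and prespecification, not validity. Centre is a stratification factor and is in no listed model, and the two-group comparison uses none of the three factors. For an assumed 10 to 20% of PRWE variance explained by the strata, the unadjusted standard error is about 5 to 11% too large and type I error is about 3 to 4%. Power at 11 points falls by about 2 points (about 2 to 3 at 30%). Leaving out centre alone costs roughly 1 to 1.5 points when centre explains 10 to 20%. With no stratum effect nothing is lost. These sizes rest on assumed stratum effects, age bands, block size and centre shares.

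Separately, and without any assumption, the Statistical analysis section does not fix the test for the primary outcome. It makes the choice depend on skewness while declaring PRWE normal, and one of the two tests does not address the mean difference used for the sample size.

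**What to change.** - Name one primary analysis of PRWE, applied whatever the skewness: a linear model with cast, centre, age and intra- or extra-articular fracture line. Report the adjusted mean difference with a 95% confidence interval, using robust or bootstrap standard errors so that normality is not required.
- Keep Mann-Whitney as a sensitivity analysis.
- Add centre to the existing multivariable regression, and say whether fracture group there means the stratification factor.
- Delete the clause "since the outcome variable PRWE is normally distributed".
- In the Follow-up section, say that stratified randomisation guards against centre imbalance and that centre is also included in the analysis.

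The cost is analysis wording only. The three factors are known at randomisation, so no new data are needed, and three centres use two degrees of freedom.
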